### Study setting

Dak Lak province is located in the Central Highlands of Vietnam (see Fig. 2), and has a population of approximately 1.9 million [25]. The province is comprised of one provincial city (Buôn Ma Thuột), one district-level town (Buôn Hồ), and 13 districts. Together, the provincial city, district-level town, and districts are comprised of 182 communes, wards and towns, with each further subdivided into hamlets, generally comprising between 100 and 1000 households. The trial will take place in all 13 districts.

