### Selection and randomisation of clusters

Schools are eligible to participate in the study if they meet the following criteria:
Defined by the Department of Education and Training as a primary school (grades 1–5)Have between 200 and 450 students enrolled (due to sample size requirements and operational constraints)Located in a rural, remote, or very remote area, as defined by Department of Education and Training.

In June 2019, a list of schools meeting these criteria was generated with assistance from the Department of Education and Training. Out of 423 primary schools in Dak Lak province, 129 met eligibility criteria, and 64 were randomly selected from this list, stratified by district to ensure good geographic coverage. To ensure that no study schools shared hamlets in their catchment areas, no more than one school was selected from a given commune. The remaining 65 eligible schools were retained as potential replacement schools.

Selected study schools and replacement schools were randomised 1:1 to the control and intervention arms, stratified by district. Randomisation was performed by an independent, blinded statistician, using a computerised random number generator.

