### Sample size calculation

Sample size calculations were based on the primary outcome, prevalence of hookworm infection. To estimate the number of clusters required, we used our previously published generalised linear model to predict the impact of mass and targeted deworming on prevalence reduction in school-age children [20]. Assuming a baseline hookworm prevalence of 20%, the model predicts a relative prevalence reduction of 79% after mass deworming and 45% after targeted deworming, measured 12 months after one round of deworming. Assuming an average cluster size of 120 children in the target age group and an intra-cluster correlation coefficient of 0.12 [31], with a power of 80% and α = 0.05, the sample size required to detect this reduction or greater as significant is 64 primary schools, randomised 1:1 between the two study arms. Given the predicted low starting prevalences of *A. lumbricoides* and *T. trichiura*, the study is not powered to detect a difference between study arms for these STH.

To achieve the required sample size of 120 participants per cluster, we will initially aim to recruit at least 180 participants per cluster. This will allow for a loss to follow-up of up to 30%. The estimated total number of participants in data collection is 7680.

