### Statistical analysis

Intention-to-treat analyses will be conducted to compare study outcomes between the intervention and control arms. Unadjusted analyses will involve comparing infection prevalence and intensity between study arms at study follow-up, using univariable regression analyses accounting for clustering by school. For adjusted analyses, generalised linear and non-linear mixed models will be used to account for within and between cluster variability. For infection prevalence, the outcome will be the infection status of the individual, so Bernoulli logistic regression will be used. For infection intensity, linear regression models will be used. For all models, age and sex will be entered as covariates (fixed effects), and school as a random effect. The intervention will be entered as a binary fixed effect to estimate differences in prevalence and intensity, and a relative risk of infection, comparing the two arms at each follow-up survey. All analyses will be conducted using a 5% level of significance.

Baseline characteristics will be compared between the intervention and control arms using descriptive statistics. If there is a need to adjust for differences in the baseline characteristics of the intervention and control groups, additional analyses will be conducted incorporating variables measured in the study questionnaires as covariates, allowing an adjusted effect estimate to be calculated for the intervention.

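### Schools were randomised within district, but the models fixed in the protocol have no district term; if districts differ, the hookworm test is conservative and loses some precision

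*Protocol article*

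**What the plan says.** Under Selection and randomisation of clusters, the protocol states: "Selected study schools and replacement schools were randomised 1:1 to the control and intervention arms, stratified by district". Study setting fixes the number of strata: "The trial will take place in all 13 districts".

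The Statistical analysis section sets out two analyses. The unadjusted one compares arms at follow-up "using univariable regression analyses accounting for clustering by school". For the adjusted one, the terms are listed: "For all models, age and sex will be entered as covariates (fixed effects), and school as a random effect", with intervention as a binary fixed effect. If baseline characteristics differ between arms, "additional analyses will be conducted incorporating variables measured in the study questionnaires as covariates". The level is fixed too: "All analyses will be conducted using a 5% level of significance". District appears in none of these analyses.

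The Sample size calculation section, planned "with a power of 80% and α = 0.05", makes no allowance for stratification either.

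**The concern.** Allocating schools 1:1 within district makes the arms nearly equal in district composition. Differences between districts then largely cancel out of the arm contrast, and its true sampling variance is smaller than under unrestricted allocation. A model with only a school random effect does not use this. It counts district differences as between-school noise and reports a standard error for a design that was not used.

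The consequence is an interval that is too wide and a test that rejects less often than 5% under the null. Part of the precision that stratification provides is not claimed.

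The optional covariate step does not repair this. It is triggered by baseline imbalance, which stratification is meant to prevent for district. It also draws on questionnaire items, which the Data collection section describes as hygiene and defecation practices, water source, home environment and socioeconomic status.

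Nor is this a detail that the article simply leaves to an analysis plan. It lists the terms for all models, so an analyst who follows it leaves the stratum out.

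**Working it through.** **Inputs from the protocol.** "Assuming a baseline hookworm prevalence of 20"%, with relative reductions of 45% (targeted) and 79% (mass), gives 0.20 × 0.55 = 0.110 and 0.20 × 0.21 = 0.042 at 12 months. Cluster size is 120, the intra-cluster correlation is 0.12, and there are 32 schools per arm.

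**Assumptions.** Tests are two-sided. The 64 schools split as 12 districts of five and one of four. A share s of the between-school variance lies between districts. The protocol gives neither the split nor s.

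**Step 1: reproduce the planned size.** The design effect is 1 + 119 × 0.12 = 15.28. Two proportions of 0.110 and 0.042 at 80% power need 238 per arm (pooled variance, no continuity correction). Then 238 × 15.28 / 120 = 30.3, so 31 schools per arm and 62 in total, within two of the stated 64. At 32 per arm, power is 82.2% (normal) or 81.5% (t on 62 df).

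**Step 2: standard error without stratification.** The effective number per arm is 32 × 120 / 15.28 = 251.3. The standard error is √[(0.110 × 0.890 + 0.042 × 0.958) / 251.3] = √(0.1381 / 251.3) = 0.0234.

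**Step 3: true variance under stratified allocation.** A five-school district splits 3:2, so it leaves a net weight of ±1/32 in the contrast; the four-school district leaves none. The district part therefore keeps 12/1024 of its variance instead of 64/1024. The true variance, relative to step 2, is (1 − s) + (12/64)s = 1 − 0.8125s.

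**Step 4: variance reported by a model without district.** Within an arm of 32 there are 496 pairs of schools. Pairs from the same district number 6 × 3 + 6 × 1 + 1 = 25. The expected reported variance, relative to step 2, is 1 − (25/496)s = 1 − 0.0504s, so it hardly moves.

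**Step 5: ratio and test level.** The reported standard error exceeds the true one by the factor r = √[(1 − 0.0504s) / (1 − 0.8125s)]. The actual level is about 2P(t₆₂ > 1.999r). At s = 20%, r = √(0.9899 / 0.8375) = 1.087 and the level is 3.4%.

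**Step 6: simulation of school means under the same inputs** (15,000 null and 6,000 alternative runs per share). The analysis without district used t on 62 df; the analysis with district fixed effects used t on 50 df.

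| s | Mean reported SE | True SD | SE too large by | Type I without district | Type I with | Power without | Power with |
|---|---|---|---|---|---|---|---|
| 0 | 0.0233 | 0.0234 | none | 4.9% | 4.8% | 81.6% | 79.5% |
| 10% | 0.0233 | 0.0225 | 4% | 4.1% | 4.9% | 82.7% | 83.7% |
| 20% | 0.0232 | 0.0214 | 8% | 3.4% | 4.6% | 84.4% | 87.8% |
| 30% | 0.0232 | 0.0204 | 14% | 2.6% | 5.0% | 85.2% | 91.7% |
| 50% | 0.0230 | 0.0181 | 27% | 1.4% | 4.9% | 88.2% | 97.9% |

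The formulas in steps 3 to 5 give r = 1.041, 1.087, 1.141 and 1.281 and levels of 4.2, 3.4, 2.6 and 1.3% at the four non-zero shares, in agreement with the simulation.

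**Step 7: binary outcomes.** A second simulation drew binary outcomes with logit-normal school effects and analysed school-level log-odds. Without district, type I error was about 5, 4, 3.6, 3 and 1.6 to 1.9% across the same shares; with district it was about 5%. Absolute power was higher in that model, but the pattern was the same.

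**Step 8: the remedy under the planned model type.** The protocol plans a logistic mixed model and does not name the estimation method, so maximum likelihood is an assumption here. Fitting 12 extra cluster-level parameters to 64 schools biases the school variance downwards. The Gaussian analogue of a Wald z test is 2P(t₅₀ > 1.96 × √(50/64)) = 8.9%, against 2P(t₆₂ > 1.96 × √(62/64)) = 5.8% without district. A simulation of the logistic mixed model by adaptive quadrature (school SD 1.2 on the logit scale, 2,000 null runs, age and sex omitted) gave 8.5 to 9.2% with district fixed effects. Without district it gave 5.6 to 5.9% at s = 0 and 4.0 to 4.1% at s = 20%. A district random intercept brought the level to about 6 to 7%, and a small-sample t reference to about 5 to 6%.

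**The case against.** Four objections deserve weight.

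*The effect is conditional.* The protocol does not give the district share. Its preliminary survey reports school prevalences from 3.2 to 55.2% in 13 schools, which could arise entirely within districts. The reason it gives for stratifying the selection of schools is geographic coverage; it does not call district prognostic. This stands: at s = 0 nothing is miscalibrated, and the larger shares in the table are scenarios, not estimates.

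*The error is on the safe side.* This also stands. Leaving out a balanced stratification factor makes the test conservative and creates no extra false positives.

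*The trial is not underpowered.* A reader might infer from the lost power that the trial misses its 80% target, or that stratification has been wasted. The protocol's own inputs support neither. Power without district is 81.6% at s = 0 and rises to 88.2% at s = 50%, because balance helps even when the model ignores it. The loss is relative to an analysis that includes district.

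*The obvious remedy can do harm.* Simply adding district fixed effects to a logistic mixed model fitted by ordinary maximum likelihood would replace a mildly conservative test with an anti-conservative one, at about 9%. This stands and shapes the fix.

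None of these removes the mismatch itself: the design stratifies by district, and the fixed model terms leave district out.

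**Conclusion.** The point holds as a conditional flaw of efficiency and calibration, of moderate weight. If districts differ in hookworm prevalence, the models as written overstate the standard error of the primary contrast: by about 4% if a tenth of between-school variance lies between districts, and about 27% if half does. The matching loss of power is about 1 to 10 points.

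The direction needs only the stratified allocation and some district variation. The size rests on the assumed district share, the assumed split of schools across districts and the protocol's intra-cluster correlation of 0.12. The documents do not support the stronger conclusion that the primary result would be invalid.

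**What to change.** Before follow-up data are seen, amend the Statistical analysis section so that district, the randomisation stratum, is accounted for in both the primary hookworm model and the unadjusted comparison. Two forms are acceptable:

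- a district random intercept alongside the school random effect; or
- district fixed effects.

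In either case, state a small-sample degrees-of-freedom correction of about 50 df (64 schools − 13 districts − 1 for arm = 50). Do not enter 12 district fixed effects under uncorrected maximum likelihood with a Wald z or likelihood ratio test.

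The cost is a sentence or two of text and no change to design or data collection. If districts do not differ, fixed effects cost at most about 2 points of power (81.6% to 79.5%) and a random intercept almost none. Fixing this in advance also avoids the appearance that district was added after seeing the results.

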### Study outcomes

The primary outcome is the prevalence of hookworm infection (unspeciated) detected using qPCR, 12 months after deworming. Secondary outcomes are prevalence of *N. americanus*, *A. duodenale*, *A. ceylanicum* (i.e. species-specific hookworm infections), *Ascaris* spp., and *T. trichiura* by qPCR; mean intensity of hookworm infection, calculated as the average number of eggs per gram of faeces; treatment coverage with albendazole (i.e., the proportion of eligible schoolchildren and community members who receive albendazole); and adverse events following albendazole distribution.

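### The planned logistic mixed model is said to give a prevalence difference and a relative risk, but its arm term is a school-conditional log odds ratio and no conversion is stated

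*Protocol article*

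**What the plan says.** The Study outcomes section defines a binary primary endpoint: "The primary outcome is the prevalence of hookworm infection (unspeciated) detected using qPCR, 12 months after deworming".

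The Statistical analysis section fixes three features of the adjusted analysis:

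- Model: "the outcome will be the infection status of the individual, so Bernoulli logistic regression will be used".
- Terms: "age and sex will be entered as covariates (fixed effects), and school as a random effect".
- Purpose of the arm term: "The intervention will be entered as a binary fixed effect to estimate differences in prevalence and intensity, and a relative risk of infection".

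The section mentions no odds ratio, no log or identity link for infection status, and no step from the logistic fit to a risk scale. The unadjusted analysis is described only as univariable regression that accounts for clustering by school, with no link given.

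The Sample size calculation section expresses the expected effects as relative changes in prevalence: "the model predicts a relative prevalence reduction of 79% after mass deworming and 45% after targeted deworming".

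**The concern.** In a logit-link model with a school random intercept, the arm coefficient compares the log odds of infection between arms at a given value of the school effect. Two things separate its exponential from the relative risk. An odds ratio lies further from 1 than the corresponding risk ratio. Conditioning on the school effect then moves it further from 1 again. Both shifts go in the same direction and, for a beneficial intervention, make it look better. A prevalence difference cannot be read from this coefficient at all.

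Followed literally, then, the stated rule does not produce the stated measures. What is at stake is the size of the primary effect as reported, and whether it can be set beside the relative prevalence reductions used in planning.

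**Working it through.** **Inputs (Sample size calculation section).** Baseline prevalence 20%; relative reductions 45% (targeted) and 79% (mass); 120 children per cluster; intra-cluster correlation (ICC) 0.12, scale not stated; power 80%; alpha 0.05, taken here as two-sided; 64 schools, 1:1.

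**Step 1. Planning prevalences.**
- Control: 0.20 × (1 - 0.45) = 0.110.
- Intervention: 0.20 × (1 - 0.79) = 0.042.

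**Step 2. Reproduce the plan's own figure.** Comparing 0.110 with 0.042 needs 238 children per arm under individual randomisation. The design effect is 1 + (120 - 1) × 0.12 = 15.28. Then 238 × 15.28 / 120 = 30.3 clusters, rounded up to 31 per arm. Adding the customary one cluster per arm gives 32, or 64 in total. A cluster formula with between-cluster variance ICC × p(1 - p) gives 31.09, also 32 per arm. The stated 64 is reproduced, so 0.110 and 0.042 are a fair reading of the planning assumptions.

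**Step 3. The measures the plan promises.**
- Relative risk: 0.042 / 0.110 = 0.382, a 61.8% reduction.
- Difference: 0.042 - 0.110 = -0.068, or -6.8 points.

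**Step 4. Marginal odds ratio.** (0.042 / 0.958) / (0.110 / 0.890) = 0.355.

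**Step 5. Odds ratio estimated by the planned model.** Let the school effect be normal with variance s². In each arm, solve for the intercept b at which the average of 1 / (1 + exp(-(b + u))) over u ~ N(0, s²) equals that arm's prevalence, by Gauss-Hermite quadrature. The conditional odds ratio is exp(b_intervention - b_control). Because the ICC scale is not stated, three readings are shown.

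| Reading of ICC 0.12 | s² | Conditional OR | Apparent reduction if read as a relative risk |
|---|---|---|---|
| Latent logit scale: s² = 0.12 × (π²/3) / 0.88 | 0.449 | 0.343 | 66% |
| Proportion scale, control-arm prevalence | 1.25 | 0.319 | 68% |
| Proportion scale, mean of the two prevalences (7.6%) | 1.56 | 0.310 | 69% |

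Against the true 62%, the overstatement is about 4 to 7 percentage points of relative reduction. On the log scale, ln(0.343) / ln(0.382) = 1.11 and ln(0.310) / ln(0.382) = 1.22, so the coefficient is 11% to 22% too large if taken as a log relative risk.

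**Step 6. Does the choice of conversion matter?** Take s = 1.12 (the second row).
- Averaging predicted risks over the school effect returns 11.0% and 4.2%: relative risk 0.382, difference -6.8 points.
- Predicting with the school effect set to zero gives 7.4% and 2.5%: difference -4.9 points. That is (6.8 - 4.9) / 6.8 = 28% too small.

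The same fitted model can therefore overstate the relative effect or understate the absolute one, depending on a step the article does not name.

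**The case against.** The strongest reply is that a model is more than one coefficient. A logistic mixed model with an arm term can yield both promised measures from predicted risks averaged over schools and covariates, as step 6 shows. The promise of a prevalence difference even suggests that some post-estimation step is intended, since nobody could read a difference from a logit coefficient. Standardisation and interval methods are also details that a journal article may leave to a fuller document, which is not at hand.

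Much of this stands. The model need not be replaced, and the lack of computational detail would not by itself be a finding. What remains is that the article names the link, the random effect, the term and the quantities that term is to estimate, and these do not match. A later document could supply the conversion, but the published sentence would still be wrong as it reads.

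Three stronger readings should be set aside.

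- A reader might infer that the trial will report an odds ratio under the name of relative risk. The article never says that the exponentiated coefficient will be reported in this way.
- A reader might infer that the error carries into the cost-effectiveness results. The Cost-effectiveness analyses section rests the 12-month analysis on outcomes observed in the trial and takes longer-term health outcomes from a transmission model. It does not say that this regression supplies an input.
- A reader might infer a large distortion from the fact that the gap widens with prevalence. With the two reductions held fixed, the marginal odds ratio alone would be 0.30 against a relative risk of 0.38 at 55% baseline prevalence. But the article plans on 20% and expects a fall in both arms, so the planning-value range is the relevant one.

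**Conclusion.** The point holds as a mismatch between the stated model term and the stated effect measures, at moderate severity. At the planning prevalences, the arm term corresponds to a school-conditional odds ratio of about 0.31 to 0.34, where the relative risk is 0.382 and the difference is -6.8 points. The consequence, a 66% to 69% reduction shown where 62% is true, is conditional: it arises only if the coefficient is taken at the article's word as a relative risk.

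The figures assume a normal school effect with the same variance in both arms, no covariate effects, and the article's planning prevalences. The spread reflects the unstated scale of the ICC. The choice of 64 schools is not affected, and the test of no effect barely changes.

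**What to change.** Amend the Statistical analysis section along these lines:

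1. Keep the logistic mixed model for the test of the arm effect, and call its exponentiated coefficient a school-conditional odds ratio.
2. State that the relative risk and prevalence difference come from the same model. For each arm, predict every child's risk as if allocated to that arm, integrate over the estimated school-effect distribution rather than setting the effect to zero, and average over the observed ages and sexes. Then take the ratio and difference of the two averages.
3. State how the 95% confidence intervals are obtained: a bootstrap that resamples whole schools, or the delta method.

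For the relative risk, an acceptable alternative is a modified Poisson GEE with log link, schools as clusters and robust standard errors corrected for the number of clusters. Whichever route is chosen should be fixed before outcome data are seen by arm.

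The cost is a change of wording and a few lines of code. No new data, participants or schools are needed.

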### Assessment of acceptability and feasibility

A mixed-methods study will be undertaken to identify perceptions, barriers and facilitators to community-wide deworming in Vietnam, in order to inform policymakers regarding implementation and scale-up of community-based deworming. The acceptability of school-based and community-wide deworming will be examined using a series of focus group discussions (FGDs) with community members, school headmasters, and teachers, conducted following the first round of deworming. The FGDs will take place in randomly selected schools and hamlets in both study arms, stratified by district. Purposive sampling of community members will be used, to ensure inclusion of community members across different age groups (including school-age children), socioeconomic positions, and cultural groups, and representation of both males and females. Individual semi-structured interviews will additionally be held with community leaders, school headmasters, and teachers. FGDs and interviews will explore perceptions of community-based deworming for STH control, and perceived barriers and facilitators at individual and community levels.

Feasibility of community-based deworming for STH control will be explored using individual semi-structured interviews with key stakeholders, to identify perceptions and perceived barriers and facilitators at programmatic and policy levels. Interviews will be held with national, provincial, and district-level staff of the national NTD control program, and health staff at district and commune levels.

Written informed consent will be obtained prior to FGDs and interviews, which will be conducted in Vietnamese and recorded digitally. Following completion of the FGDs and interviews, recordings will be transcribed and translated. Coding and analysis will be done using NVivo software (QSR International, Doncaster, Australia). Key themes will be identified and analysed using thematic analysis.

